**Objective:**

The overarching goal of this study is to reduce morbidity and mortality among post-MI patients through improved long-term cardiac medication adherence. The specific objectives include the following. First, we will assess whether long-term cardiac medication adherence improves among elderly, post-MI patients following the implementation of (1) standardized discharge prescription forms with 90-day prescriptions and 3 repeats for recommended cardiac medication classes, in combination with education and (2) education alone compared to (3) usual care. Second, we will assess the cost implications of prolonged initial discharge prescriptions compared with usual care. Third, we will compare clinical outcomes between longer (>60 days) versus shorter prescription durations. Fourth, we will collect baseline information to inform a multicenter interventional study.

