### Rationale and Study Objectives

Poor medication adherence was identified by the World Health Organization in 2003 as a worldwide challenge in the management of chronic diseases [17]. The consequences of suboptimal adherence include undesirable health outcomes as well as increased health care costs. Both provider-level and system-level factors play important roles in optimizing adherence. We have previously shown that inappropriate beliefs regarding risk perception and outcome expectancies, prescription refill burden, and unintentional forgetfulness due to lack of habituation all contribute to the observed general decline in medication adherence over time [18-20]. Providing longer prescriptions at the time of discharge can address all of these barriers. However, prescriptions covering ≥90 days are currently provided to only 21% of all cardiac patients and to no more than 54% of MI patients, suggesting an opportunity for this change to benefit many patients [4,21].

We know of no guidelines or practice standards for physicians that recommend the prescription of maximum duration (ie, ≥90 days) for cardiac medications at discharge. The use of standardized hospital-based medication discharge practices has been shown to minimize medication errors and to optimize guideline-recommended therapies [22]. However, no prospective study has evaluated the effects of implementing an institutional policy or standardized discharge cardiac medication prescriptions of maximum duration on long-term medication adherence. Therefore, it is hypothesized that longer prescription duration at discharge will promote better long-term cardiac medication adherence.

The specific objectives of this study include estimating and comparing the effects on long-term cardiac medication adherence of (1) a standardized discharge form featuring prescription duration of 90 days with 3 repeats in post-MI patients in combination with education, (2) education only, and (3) usual care (ie, no intervention regarding prescription duration) and assessing the economic implications of the prolonged initial discharge prescriptions as compared to usual care. To our knowledge, this project is the first interventional study to investigate how modifying prescription duration impacts medication adherence.

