### Statistical Analysis

#### Primary Outcome Analysis

Our primary analytical approach will use segmented linear regression analyses of the aggregate monthly data in each group. To promote stability of the time series, we will pool data across the hospitals within each intervention group (ie, standardized discharge prescription forms plus education [intervention group 1] or education only [intervention group 2]). Within each of the 2 intervention groups, we will then independently analyze the aggregated monthly proportions of patients adherent to their cardiac medication regimen at 1 year (expressed as a percentage) using segmented linear regression. In case of nonlinearity of the monthly series, segmented logistic regression analysis of the monthly proportions will be used. Terms will be included for time (in months; treated as continuous [range, 0-35]), intervention (an indicator denoting observations from the post-intervention window), and time post-intervention (defined as time-23 if observation from post-intervention period; 0 otherwise) [35,36]. Serial autocorrelation will be accounted for using first-order autoregressive errors. Visual assessment of model residuals plotted against time will be used to assess goodness of fit. Intervention effects estimated using segmented linear autoregressive error models will be expressed as absolute post-intervention changes in the intercept and slope with corresponding 95% CIs. Post-intervention changes in intercept (or level) and slope (or trend) can respectively be interpreted as the immediate and gradual effects of the intervention on the primary outcome over time [35,36]. Additionally, we will express the overall intervention effect (ie, as combined intercept and slope changes) at the end of the study, on the absolute scale, by comparing the fitted post-intervention trend to the projected secular trend in the final month of observation [35].

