The aforementioned segmented regression analyses will compare pre-intervention to post-intervention levels and trends within intervention groups; therefore, groups will act as their own internal controls. Additionally, we will compare these changes to changes observed in the control group (ie, all other hospitals in Ontario). Analysis of the parallel control group — which will be identically specified to the intervention group analyses — will help address threats to internal validity, such as co-occurring interventions or other policy changes that could be rival explanations for any observed changes in our intervention series. In other words, if we detect a post-intervention effect in the parallel control group, it suggests that changes in the underlying patient population or another (unidentified) intervention could have occurred around the same time across Ontario hospitals that might explain away any observed intervention effects.

To account for potential differences in patient case mix over time and among sites, we will conduct additional secondary analyses of the primary outcome with the patient as the unit of analysis. We will use segmented binary logistic regression analysis with terms as specified in previous paragraphs and with the addition of the following patient covariates: age, sex, type of MI (STEMI vs non-STEMI), prior MI, prior cardiac medication use, and site.

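### The objectives are between-group, but every effect with a stated confidence interval is within-series; the promised comparison with control has no defined contrast, and none is described between the two packages

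*Protocol article*

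**What the plan says.** **The question.** The abstract's Objective asks whether adherence improves with form plus education and with "education alone compared to (3) usual care". Rationale and Study Objectives goes further: "The specific objectives of this study include estimating and comparing the effects on long-term cardiac medication adherence of" the form with education, education only, and usual care.

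**The primary model.** Primary Outcome Analysis states: "Within each of the 2 intervention groups, we will then independently analyze the aggregated monthly proportions". The regressors are listed: "Terms will be included for time (in months; treated as continuous [range, 0-35]), intervention (an indicator denoting observations from the post-intervention window"), and time since the intervention. There is no group term and no interaction with group.

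**The effect measures.** Effects are "expressed as absolute post-intervention changes in the intercept and slope with corresponding 95% CIs". The overall effect is obtained "by comparing the fitted post-intervention trend to the projected secular trend in the final month of observation", so its reference is the group's own projected trend.

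**The control.** The article says each group is its own internal control. It adds that the changes will be compared with those in all other Ontario hospitals, using a model of the same specification. It then explains this comparison: "if we detect a post-intervention effect in the parallel control group, it suggests that changes in the underlying patient population or another" intervention may have occurred at about that time and might account for the result.

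**Patient-level analyses.** These reuse the same segmented terms and add covariates, including site. Site moves the baseline; it does not give a contrast of the intervention change between groups.

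**Power.** The 80% is for a 10-point level change in each of the two intervention groups.

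**The concern.** A change measured against a group's own past is the effect of the package plus whatever else changed in the province in September 2017. The six intervention sites are a convenience sample, so the control series is the main protection against that second component. Reading the control by whether a change is detected does not remove the component from the estimate, and it depends on how many patients the control happens to contain. A small control series can miss a shift that matters, and a large one can flag a shift too small to explain a 10-point effect. Nor does a significant change in one series and a non-significant change in another test the difference between them.

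At stake are the two headline statements that the study wants to make: how much each package improves adherence over usual care, and what the form adds to education.

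**Working it through.** **Inputs from the protocol article.** 24 monthly points before and 12 after; time coded 0-35; time since intervention coded as time minus 23; first-order autoregressive errors (Primary Outcome Analysis). Baseline adherence 75%, autocorrelation 0.3, 10-point level change, 5% level, 60 patients a month per site (Power Calculation). Group 1 has 2 sites and group 2 has 4 (Groups).

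**Assumptions.** Monthly variance is binomial, 0.75 × 0.25 / n = 0.1875 / n. The control volume is not given, so 300, 600 and 1,000 patients a month are tried. A provincial level shift of 3 points occurs at the intervention date. Series are independent, and normal approximations are used.

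**Step 1: standard error of a level change.** Generalised least squares for this design gives SE = 0.8655 × √(0.1875/n).

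| n per month | SE (points) |
|---|---|
| 60 | 4.84 |
| 120 | 3.42 |
| 240 | 2.42 |
| 300 | 2.16 |
| 600 | 1.53 |
| 1,000 | 1.19 |

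**Step 2: the plan's own figure.** Within-group power for 10 points is 54% at n = 60 and 83% at n = 120 (Wald). The stated 80% is not matched exactly by either. The printed inputs are ambiguous (0.1875/60 = 0.0031, against a stated mean square error of 3.1%; per site against pooled group). That is a separate matter. What counts here is that the 80% is for a within-group change under any reading.

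**Step 3: how often the control change is significant under a 3-point shift** (two-sided 5%).
- 300 a month: 3/2.16 = 1.39, probability 28%.
- 600 a month: 3/1.53 = 1.96, probability 50%.
- 1,000 a month: 3/1.19 = 2.53 (unrounded SE 1.185), probability 72%.

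In every case the expected within-group estimate contains the whole 3 points.

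**Step 4: cost of estimating the difference from control.** SE of the difference = √(SE_group² + SE_control²), so the interval widens by the factor √(1 + n/N), where N is the control volume.

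| Group volume | N = 1,000 | N = 600 | N = 300 |
|---|---|---|---|
| 60 | 3% | 5% | 10% |
| 120 (group 1, if 60 is per site) | 6% | 10% | 18% |
| 240 (group 2, if 60 is per site) | 11% | 18% | 34% |

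**Step 5: group 1 against group 2, 10 points.**
- 60 a month each: SE = √(4.84² + 4.84²) = 6.84; 10/6.84 = 1.46; power 31%.
- 120 and 240 a month: SE = √(3.42² + 2.42²) = 4.19; 10/4.19 = 2.39; power about 67%.

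**The case against.** **A comparison is promised.** The article says in plain words that the changes will be compared with those in the control group. A reader might infer that the control serves only as a detection check and that the comparison is never made. The text does not support those absolutes. What stands against the plan is that the promised comparison has no estimand, model term, interval or test, and that the only explanation offered is in terms of detection.

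**No formal gate is stated.** A reader might also infer a rule by which a significant control result overturns an intervention effect. The wording is hedged: a control effect is suggestive and might explain the finding. No threshold or discard rule is set. The percentages in Step 3 therefore show how informative detection is, not the error rate of a stated decision rule.

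**The contrasts can be derived.** With independent series and identically specified models, a difference and its standard error follow by subtraction, and a fully interacted stacked model does little more. This is right, and it means that the contrasts are obtainable, including package against package. But the article does not commit to reporting them or to resting its conclusions on them.

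**A condensed article may leave detail to an analysis plan.** It may, but this one gives the primary model term by term, with coding, error structure, effect measures and the reading of the control. What it fixes does not answer the question it poses.

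**Package against package may be secondary.** The abstract compares each package with usual care; only the Rationale wording extends to all three conditions. This supports treating that contrast as a further one, not as the main one.

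**Conclusion.** The point holds as a mismatch between the objectives and the analysis. The objectives are between-group, every effect with a stated interval is within-series, the comparison with control is promised without being defined, and no comparison of group 1 with group 2 is described. As written, the reported effect includes the full size of any concurrent provincial change. Detection in control would reveal a 3-point shift in only 28% to 72% of studies.

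That range rests on an assumed shift, assumed control volumes, binomial variance and autocorrelation 0.3. The inclusion of any shared shift in the within-group estimate does not depend on these figures. A single power figure for group 1 against group 2 should not be quoted: it runs from about 31% to 67%, depending on whether 60 patients a month is per group or per site.

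**What to change.** In Primary Outcome Analysis:
- Add one stacked (controlled) segmented regression of the three monthly series, with group-by-time, group-by-intervention and group-by-time-post-intervention terms, and group-specific AR(1) and variance.
- Report differences in level change, slope change and end-of-study effect, each with a 95% CI. Group 1 v control and group 2 v control should be the basis for the conclusions, with group 1 v group 2 as a further contrast.
- Keep the single-group fits as descriptive.
- Replace the reading of the control by detection with these estimated differences.

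In Power Calculation, state that the 80% applies to within-group changes.

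**Cost.** Analysis wording and one more model on data already planned. The price in precision is the widening in Step 4. Power against control for 10 points is correspondingly lower than within-group power, and the package contrast may be imprecise.

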#### Secondary Outcome Analysis

Consistent with the secondary analyses of the primary outcome described in the preceding section, all secondary outcomes will be analyzed using patient-level segmented regression analyses with terms for time, intervention, time after intervention, and the following covariates: age, sex, type of MI, prior MI, prior cardiac medication use, and site. The remaining secondary outcomes (time to hospitalization for cardiovascular disease, hospitalization due to repeat acute MI, hospitalization due to stroke, repeat cardiac catheterization, coronary revascularization, and death) will be analyzed at the patient level using Cox proportional hazards regression. Death will be treated as a censoring event for analyses of nonfatal, time-to-event outcomes.

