#### Power Calculation

Using the simulation approach developed by Zhang et al [37], we determined that 24 pre-intervention and 12 post-intervention data points (collected at monthly intervals) in each of the 2 intervention groups will achieve 80% power to detect an immediate absolute increase (ie, intercept change) of 10% in the monthly proportion of patients deemed adherent to their recommended cardiac medications using a likelihood ratio test at the 5% level of significance. The anticipated baseline proportion of patients with cardiac medication adherence (ie, average PDC ≥80%) is 75%. The simulation assumed a mean square error for the monthly proportions of 3.1% with 60 patients per month per site, a pre-intervention trend of 0, and an autocorrelation parameter of 0.3.

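### The patient-level segmented models make no provision for the serial correlation that the primary model and power calculation assume; if it persists after adjustment, ordinary intervals for the adherence effects are too narrow

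*Protocol article*

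**What the plan says.** In the protocol article, Primary Outcome Analysis, the main model is a segmented linear regression of the aggregated monthly adherence percentages in each group. Its terms are listed in one sentence: "Terms will be included for time (in months; treated as continuous [range, 0-35]), intervention (an indicator denoting observations from the post-intervention window" and a time-since-intervention term. A separate sentence gives the error structure: "Serial autocorrelation will be accounted for using first-order autoregressive errors". The reporting sentence ties that structure to the aggregate linear models: "Intervention effects estimated using segmented linear autoregressive error models will be expressed as absolute post-intervention changes in the intercept and slope".

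Later in the same section the plan changes the unit of analysis: "we will conduct additional secondary analyses of the primary outcome with the patient as the unit of analysis". The model is described as follows: "We will use segmented binary logistic regression analysis with terms as specified in previous paragraphs and with the addition of the following patient covariates". The covariates are age, sex, type of MI, prior MI, prior cardiac medication use and site.

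Secondary Outcome Analysis repeats the form: "all secondary outcomes will be analyzed using patient-level segmented regression analyses with terms for time, intervention, time after intervention, and the following covariates" are the same six. Clinical events are analysed by Cox regression.

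Power Calculation assumes "an autocorrelation parameter of 0.3" for the monthly adherence proportions. Neither description of the patient-level models mentions serial correlation, a month effect or a robust variance. Neither states that patients are taken as independent.

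**The concern.** If monthly adherence proportions are autocorrelated, patients discharged in the same or neighbouring months share something that the regression does not explain. The intervention and time-since-intervention terms take one value per calendar month, so these are the coefficients whose standard errors depend on that shared component. Site is a fixed covariate and cannot absorb shocks that come and go by month.

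The autoregressive error cannot simply be carried over either. A binary patient-level likelihood with many patients per month has no residual series to which an AR(1) process attaches, so some other device is needed and none is named. Run from its listed terms, the model is an ordinary logistic regression.

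The adjusted analysis is the plan's check on case mix, and readers will set it beside the primary result. It could reach significance where the primary model does not, only because it ignores dependence that the primary model allows for.

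**Working it through.** **Inputs.** From Primary Outcome Analysis: 36 months coded 0 to 35; intervention indicator = 1 from month 24; time since intervention = month − 23 after the start, otherwise 0. From Power Calculation: 24 pre and 12 post points, autocorrelation 0.3, baseline adherence 75%, 60 patients per month per site.

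**The plan's own figure.** The stated 80% power for a 10-point level change was not reproduced. The binomial SD for 60 patients, √(0.75 × 0.25 / 60) = 0.0559, gives 54% (two-sided Wald, correlation 0.3). Reading 3.1% as an SD gives 96%. The SD for 120 patients, 0.0395, gives 83%. The mean square error in the text is ambiguous and the simulation is not fully described, so this neither supports nor weakens the present point.

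**Step 1: correlation with the monthly variance held at the model's value.** Let X be the 36 × 4 design matrix, V have entries ρ^|i−j|, and c pick the effect (final month = level + 12 × slope).

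- Ordinary SE ∝ √(c′(X′X)⁻¹c): 0.7317 level, 0.0887 slope, 0.9037 final month.
- Correct SE ∝ √(c′(X′X)⁻¹X′VX(X′X)⁻¹c) at ρ = 0.3: 0.9049, 0.1131, 1.1858.
- Ratios: 0.9049/0.7317 = 1.237; 1.275 and 1.312 for slope and final month (from unrounded values).
- Type I error = 2 × (1 − Φ(1.96/ratio)): 11.3%, 12.4%, 13.5%.

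| Residual ρ | SE ratio: level / slope / final month | Coverage of nominal 95% interval |
|---|---|---|
| 0 | 1.00 / 1.00 / 1.00 | 95% |
| 0.1 | 1.07 / 1.08 / 1.09 | 93.2 / 92.9 / 92.7% |
| 0.2 | 1.15 / 1.18 / 1.20 | 91.1 / 90.5 / 89.9% |
| 0.3 | 1.24 / 1.28 / 1.31 | 88.7 / 87.6 / 86.5% |

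**Step 2: correlation from month effects on top of binomial noise.** Each patient enters once (Recruitment), so sampling noise is uncorrelated between months. An observed lag-1 correlation of 0.3 then needs a month-level process. If that process has autocorrelation φ, its share of the total variance is s = 0.3/φ, and total variance is 1/(1 − s) times binomial, which exceeds 1/0.7 = 1.43 for any φ below 1. The step 1 formula with V = I + [s/(1 − s)]φ^|i−j| gives:

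| φ | s | Total / binomial variance | SE ratio: level / slope / final month | Coverage |
|---|---|---|---|---|
| 0.4 | 0.75 | 4.0 | 2.50 / 2.60 / 2.69 | 56.7 / 55.0 / 53.3% |
| 0.6 | 0.50 | 2.0 | 1.80 / 1.91 / 2.03 | 72.5 / 69.6 / 66.6% |
| 0.9 | 0.33 | 1.5 | 1.34 / 1.54 / 1.74 | 85.6 / 79.8 / 74.0% |
| 0.95 | 0.32 | 1.46 | 1.19 / 1.34 / 1.49 | 90.1 / 85.7 / 81.1% |

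As φ nears 1 the process looks like a trend, which the time terms absorb. At φ = 0.99 coverage returns to 94.1 / 93.0 / 91.9%.

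Simulated segmented logistic regression without covariates (60, 120 or 240 patients per month; φ = 0.4, 0.6, 0.9; 1,000 runs each) agrees: type I error is 13.5% to 45.3% for level and 20.7% to 47.9% for slope. With no month-level process it is 4.0% to 5.5%, and the ordinary-to-true SE ratio for level is 0.96 to 1.02.

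**Step 3: would the remedies work with 36 months?** A Gaussian approximation (36 monthly values, unit sampling variance, 4,000 runs, critical value 1.96) gives these type I errors for level / slope:

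| Setting | Month effect with AR(1), REML | Newey-West, lag 3 |
|---|---|---|
| No correlation | 3.4 / 3.6% | 18.0 / 22.6% |
| ρ = 0.3, step 1 | 6.8 / 7.2% | 24.6 / 28.3% |
| φ = 0.4 to 0.9, step 2 | 7.7–9.6 / 8.7–10.4% | 25.1–26.0 / 30.0–36.5% |

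**The case against.** The strongest reply is that the article is silent here and asserts nothing wrong. It gives the form, terms and covariates of a supportive analysis, and the variance estimator is the sort of detail that a statistical analysis plan may settle. A reader might infer that the plan assumes independence or deliberately abandons the autocorrelation; the text says neither. What limits this reply is that the article does give the error structure for one model and then lists the make-up of its companion down to each covariate, without a dependence device. A model run from that list is an ordinary regression.

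Second, 0.3 is a planning value for unadjusted proportions. Shifting case mix is one source of serial correlation, and the patient-level model adjusts for it, so the residual value may be smaller or nil. That stands, and it makes the consequence conditional.

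Third, the step 1 figures hold the variance equal, which does not fit patient-level binary data if the correlation is real. That also stands. Step 2 is the coherent version, and it usually gives a larger effect.

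Fourth, a reader might conclude that every secondary interval is too narrow. The documents do not support that: 0.3 was assumed for the primary adherence measure only. Class-specific adherence is a close analogue, but no autocorrelation is given for it, nor for persistence, days supplied, visits, class counts or the Cox outcomes. Clustering the Cox models by month would not answer the point either, because it still treats different months as independent.

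**Conclusion.** The point holds conditionally. The patient-level segmented models carry over the terms of the primary model but name no way to handle month-level dependence. If the planned correlation of 0.3 survives adjustment, ordinary 95% intervals for adherence cover 88.7% (level) and 87.6% (slope) when the monthly variance equals the model's. Coverage is generally lower when the correlation reflects extra-binomial month effects: about 55% to 90% for those two terms over φ = 0.4 to 0.95. If no month-level correlation remains, the intervals are correct.

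This rests on 0.3 as a planning value, on an AR(1) form, and on reading the listed terms as the whole model. The aggregate primary analysis, including the identically specified control-group series, keeps its autoregressive errors and is unaffected. The stronger inference, that all secondary results will look too precise, is not supported.

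**What to change.** State in the plan, before analysis, how month-level dependence is handled in the patient-level segmented models. Either add a month random effect with AR(1) correlation, or use month-level HAC (Newey-West type) standard errors for the time, intervention and time-since-intervention terms. In both cases report a check of residual month-level autocorrelation.

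The random effect is the safer choice. With 36 months, 12 of them after the change, plain Newey-West errors reject too often even without correlation (step 3), so that route needs a small-sample correction. The random effect removes most of the excess error but not all of it, and a small-sample reference distribution is advisable.

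No new data are needed. Under step 1 at ρ = 0.3, intervals widen by about a quarter; under step 2, by more. If no correlation is present they hardly change, with the test slightly conservative (about 3.5% at a nominal 5%). No change to the Cox models follows from this point.
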